### Data Analysis

All data collected for descriptive purposes will be presented as means and standard deviations for all sample characteristics. All outcome variables, including changes in PA behavior, self-compassion, social support, perceived leader supportiveness, and sport commitment and enjoyment, will be analyzed using an analysis of covariance statistical design. The level of significance will be set at α=.05. Statistical analyses will be conducted using SPSS software (version 21.0; IBM Corp).

Inductive thematic analysis, as outlined by Braun and Clarke [43], will be used to analyze the interview data. Data analyses will be conducted by 2 trained researchers who will independently read the transcripts numerous times to become familiar with the data and generate initial codes by identifying important features of the data that are relevant to the study objective. Coded data will then be examined for similarities, grouped, and refined to identify potential themes [43]. Representative quotes will be used to provide evidence of the themes within the data.

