**Methods:**

Using a quasi-experimental mixed methods approach, the GUM intervention was conducted in 5 schools in British Columbia, Canada. Adolescent girls aged 11 to 15 years who were identified as at risk were included in the study. The 9-week intervention, co-delivered by a PA/health promotion–trained researcher and a registered social worker, involved a PA component and a psychosocial component with evidence-based topics addressing the concerns of the adolescent girls. The following outcomes were evaluated: PA, self-compassion, social support, leader supportiveness, and sport enjoyment and commitment. Program acceptability and satisfaction was also examined. Outcome measures were assessed at baseline (week 1), week 6, and postintervention (week 9), and interview data concerning program acceptability and satisfaction were collected at postintervention from a subsample of participants.

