### Objectives

The specific objectives of the GUM study were (1) deliver and explore the effectiveness of the 9-week GUM intervention program on the primary outcomes of PA, self-compassion, social support, and leader behavior; (2) explore the effectiveness of the 9-week GUM intervention program on the secondary outcomes of sport enjoyment and commitment; and (3) examine participant perceptions of the GUM program in terms of acceptability and satisfaction.

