^c^The Learning Climate Questionnaire was the only self-report questionnaire administered at T2. See Outcome Measures for further information.

^d^Questionnaires and a wrap-up were completed. Follow-up data were collected at T3.

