#### Perceived Leader Supportiveness

The LCQ [35] was used to assess participants’ perceptions of support provided by the program facilitators. The LCQ is a 15-item measure with values ranging from strongly disagree (1) to strongly agree (7). It provides a good indication of the support that leaders provided for the 3 psychological needs (ie, autonomy, competence, and relatedness) [35]. Research shows that when these needs are supported, higher levels of psychological well-being are evident [35]. The LCQ has been shown to have extensive internal consistency and reliability, and it provides a valid indication of perceived supportiveness among youth outside of sporting contexts [41]. The LCQ was the only self-report questionnaire that was not administered at both T1 and T3; instead, it was distributed at T2.

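### Leader behavior is a primary effectiveness outcome, but its only measure is taken once, at week 6, with no control group, so neither a change nor a program effect can be estimated

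*Protocol article*

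**What the plan says.** Under Objectives, the first aim is to "deliver and explore the effectiveness of the 9-week GUM intervention program on the primary outcomes of PA, self-compassion, social support, and leader behavior". Leader behavior is thus one of four named primary outcomes.

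Under Perceived Leader Supportiveness, the instrument is the LCQ, which captures participants' "perceptions of support provided by the program facilitators". No other leader measure appears in the article. The same section gives its timing: "The LCQ was the only self-report questionnaire that was not administered at both T1 and T3; instead, it was distributed at T2". A footnote to Table 2 agrees: "The Learning Climate Questionnaire was the only self-report questionnaire administered at T2". The Outcome Measures introduction and Table 3 also place the LCQ at week 6 alone.

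Under Data Analysis, the set of outcomes to be analyzed is described as "including changes in PA behavior, self-compassion, social support, perceived leader supportiveness, and sport commitment and enjoyment". The method given for every one of them is ANCOVA. No factor or covariate is named.

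The Discussion states that the study was exploratory and had no control group.

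**The concern.** The objective, the measurement schedule and the analysis statement do not fit together for this outcome. A change needs two measurements of the same quantity, and a baseline-adjusted ANCOVA of the usual pre-post kind needs an earlier value of the same measure. The LCQ schedule supplies neither, and no comparison arm could stand in for them.

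An analyst who follows the plan would have to drop a declared primary outcome without explanation, or substitute some other ANCOVA and report it under an effectiveness objective that it cannot serve. A statistical analysis plan could not resolve this, because the LCQ data that would be needed were never scheduled.

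**Working it through.** No sample size, power figure or other number is stated for this outcome, so there is no figure to reproduce. The check sets the schedule (Table 3) against what the stated analysis needs.

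| Outcome | Status in Objectives | Measured at | Measurements per participant | T3 − T1 change available? |
|---|---|---|---|---|
| Physical activity | Primary | Weeks 1 and 9 | 2 | Yes |
| Self-compassion | Primary | Weeks 1 and 9 | 2 | Yes |
| Social support | Primary | Weeks 1 and 9 | 2 | Yes |
| Leader behavior (LCQ) | Primary | Week 6 | 1 | No |
| Sport enjoyment and commitment | Secondary | Weeks 1 and 9 | 2 | Yes |

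**Step 1: change score.** For participant i, change = Y(i, week 9) − Y(i, week 1). For the LCQ neither term exists. With 101 participants recruited there are at most 101 × 1 = 101 LCQ scores and 0 change scores.

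**Step 2: ANCOVA adjusted for the baseline of the same measure.** The model would be Y(i, later) = intercept + factor + β × Y(i, week 1) + error. The LCQ has no week 1 value, so β has no covariate to attach to.

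**Step 3: ANCOVA with other covariates.** The plan names neither factor nor covariates, so consider the most favorable version: week 6 LCQ as the response, delivery group (9 levels) or school (5 levels) as the factor, and week 1 variables such as age or baseline physical activity as covariates. This can be fitted. Its factor term estimates differences in rated supportiveness between groups or schools. Exposure to the program equals 1 for every participant, so it cannot be separated from the intercept, and no term in the model is a program effect.

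**Step 4: reach of the problem.** The missing change affects 1 of the 4 primary outcomes. Every other quantitative outcome in Table 3 has 2 measurements.

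**The case against.** **The grammar is open.** The reference to changes in the Data Analysis sentence may attach only to physical activity, with the rest a plain list of outcome variables. A reader might infer that the plan unambiguously promises an LCQ change analysis, but the text does not settle that. The ambiguity does not remove the problem: ANCOVA still covers every outcome, objective 1 still asks about effectiveness on leader behavior, and step 3 shows that such an ANCOVA cannot answer it.

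**Some adjusted analysis is possible.** A reader might infer that nothing adjusted for baseline can be done with the LCQ. That goes too far. Adjustment for other week 1 variables is feasible, and a condensed article may leave the choice of factor and covariates to another document. What is unavailable is an LCQ baseline, an LCQ change and a program effect.

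**Whether a pre-program rating was possible.** Because the LCQ rates the program's own facilitators, one might conclude that no earlier value could ever have been obtained. The article does not say whether participants knew the facilitators beforehand, so this is inference. The point does not depend on it.

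**The other three primary outcomes.** It is tempting to say that three primary outcomes remain testable for effectiveness. They have an estimable change, but they also lack a comparator, so a change in them is not by itself an effect of the program.

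**The abstract.** It names three assessment times without saying that week 6 is for the LCQ only. This might be read as a further error. It is true of the outcome set as a whole, and the body gives the schedule clearly in several places, so it is condensation.

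**The study is exploratory.** The Discussion concedes that cause and effect cannot be determined, and no sample size or confirmatory decision in the article rests on the LCQ. This limits the harm. It does not reconcile the objective with the schedule, and the listed limitations do not mention that one primary outcome has no pre-post data.

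**Conclusion.** The point stands in a specific form. Leader behavior is declared a primary effectiveness outcome and placed in the list for ANCOVA, yet its single instrument yields one mid-program score per participant and there is no control group. No LCQ change or LCQ-baseline-adjusted analysis exists. The ANCOVA that can be computed compares groups that all received the program.

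The size is one of four primary outcomes, which cannot support the claim that objective 1 assigns to it. The conclusion rests on two readings of the article: that the LCQ is the only measure behind the term leader behavior, and that the week 6 schedule, stated consistently in four places, is what was carried out. It does not depend on how the reference to changes is parsed.

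**What to change.** Before results are reported:

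- Remove leader behavior from the primary effectiveness outcomes in objective 1, and remove perceived leader supportiveness from the change/ANCOVA list in Data Analysis. Recruitment closed in May 2019, so this must be a declared, dated and justified change and not a silent edit.
- Report the week 6 LCQ descriptively as a process measure, with its mean and 95% CI, and make no effectiveness claim from it.
- Do not use the LCQ as a covariate in the main models of the other outcomes. It is measured after the program began, so adjusting for it could absorb part of the change being studied.

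No new data are needed. The cost is one fewer primary outcome and a post-recruitment change to the outcome list that has to be documented and explained in the results paper.

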## Methods

### Study Design

The GUM study protocol was prepared according to the Standard Protocol Items: Recommendations for Interventional Trials (SPIRIT) guidelines [31] and used an exploratory quasi-experimental pretest-posttest design. Data collection occurred at baseline (T1), week 6 (T2), and postintervention (T3) and included self-report questionnaires and semistructured interviews. Recruitment for the GUM program began in December 2017 and was completed in May 2019. Figure 1 provides a flow diagram of the GUM protocol, and Table 1 provides a detailed description of relative program recruitment dates.

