### Participants, Setting, and Recruitment

Participants of the GUM study included adolescent girls from 5 middle schools in British Columbia, Canada, who were aged 11 to 15 years and identified as at risk. Guidance counselors from each middle school used these criteria to identify girls and invite them to participate, encouraging those whom they felt would benefit from participating in the program. The guidance counselors were exclusively responsible for recruitment because they had previous history working with the girls on a regular one-to-one basis due to the girls’ behavioral inadequacies, issues with home life, or mental health–related concerns such as anxiety or depression. Counselors then provided interested individuals with further detailed information about the program (including parental consent and student assent forms) and prompted the students to discuss the program with their parents or guardians. Participants were asked to return the signed consent and assent forms to the guidance counselor or the research team prior to the start of the program or at T1. There were no specific exclusion criteria except that participants could not have been a participant of the previous pilot study, Girls on the Move (GoM) which took place from 2015 to 2016 [32]. A total of 101 participants forming 9 groups were recruited from 5 schools throughout the region, with group sizes ranging from 7 to 14 participants per school. Each group had a different start date, with some groups in different schools running simultaneously. However, no two groups from the same school received the intervention at the same time. Recruitment was completed in May 2019.

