The GUM intervention was designed with these specific elements in mind. By providing a safe space for at-risk adolescent girls to talk about their issues and engage in fun, organized PAs that help emphasize the importance of a physically active lifestyle, the intervention’s outcomes may be highly valuable to future research. However, this study does pose some potential limitations as a result of its noncontrolled environment, the population being studied, and the constraints based on budget and resources. First, the use of subjective self-report measures may be problematic, as the ability to recall PA engagement and other psychological factors can be imperfect among adolescents [45,46]. Second, this study was exploratory in nature and did not include a control group. Therefore, a true cause and effect cannot be determined and the outcomes may have been a result of some unforeseen variables. Additionally, the outcomes from this study will provide an estimate/exploration of effectiveness immediately after the completion of the intervention and do not include long-term follow-up, making it difficult to be certain of sustained behavior change. Lastly, the fact that the GUM study was specifically targeting at-risk adolescent girls means that the findings are only generalizable and applicable to this specific population.

In conclusion, given the lack of research around at-risk adolescents, the overarching goals and objectives of the GUM program may provide the current literature with promising results and aid in the future design and refinement of effective PA programs for at-risk adolescent girls.

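### ANCOVA, the only quantitative method named, does not by itself test T1–T3 change in a single-arm study, and it cannot test change in the LCQ, which is measured once

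*Protocol article*

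**What the plan says.** The protocol article's Data Analysis section covers "All outcome variables, including changes in PA behavior, self-compassion, social support, perceived leader supportiveness, and sport commitment and enjoyment", and says that these "will be analyzed using an analysis of covariance statistical design". It adds: "The level of significance will be set at α=.05". It names no factor, covariate or time contrast. The thematic analysis in the same section applies to the interviews only.

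The design is described elsewhere:
- Study Design: the study "used an exploratory quasi-experimental pretest-posttest design".
- Participants, Setting, and Recruitment: "A total of 101 participants forming 9 groups were recruited from 5 schools". All nine groups in Table 1 received the program.
- Discussion: "this study was exploratory in nature and did not include a control group".
- Objectives: the first aim is to deliver the program and to "explore the effectiveness of the 9-week GUM intervention program on the primary outcomes", which include leader behavior.
- Table 3: physical activity, self-compassion, social support, and sport commitment and enjoyment are measured at weeks 1 and 9.
- Perceived Leader Supportiveness: "The LCQ was the only self-report questionnaire that was not administered at both T1 and T3". It was given at T2, and Table 3 lists it at week 6 only.

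**The concern.** ANCOVA ordinarily compares group means after adjusting for a covariate. Here every girl received the same program, so there is no treatment contrast. With one arm, objectives 1 and 2 can be addressed only by asking whether scores moved between T1 and T3, and the method named does not identify that comparison.

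An analyst who follows the sentence could report a p-value that answers a different question. It could be significant when nothing changed, or insensitive to a change that every group shared. As this is the only quantitative analysis behind objectives 1 and 2, the main results depend on how one underspecified sentence is read. For leader supportiveness, which is a primary outcome, no reading yields a change.

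**Working it through.** The article gives no sample-size or power figure to reproduce. The Table 1 group sizes do agree with the total: 13+11+13+9+7+14+10+11+13 = 101.

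**Assumptions.** The documents give no SD, T1–T3 correlation or dropout. For illustration: a 1–5 scale with mean 3 and SD 0.7 at both times; correlation r of 0.4, 0.6 or 0.8; true change of 0, 0.3 or 0.5 SD; age uniform from 11 to just under 16; all 101 girls analysed; no dropout and no clustering. Each setting had 1,500 simulated studies at two-sided α=.05.

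**Reading 1: baseline as covariate, no factor.** There are two tests.
- Slope. With T3 as outcome it is r × SD(T3)/SD(T1), so its test asks whether T1 and T3 are correlated. It rejected in 99–100% of runs at every size of change.
- Uncentred intercept. This is the prediction at a baseline score of 0, which is off the scale. With no true change it equals 3 − 3r, that is 1.8, 1.2 and 0.6 for r = 0.4, 0.6 and 0.8. At r = 0.8 its standard error is about 0.7 × √(1 − 0.64) × √(1/101 + 9/(100 × 0.49)) = 0.42 × 0.44 = 0.185, so the ratio is 0.6/0.185 ≈ 3.2. The test rejected in 100%, 99.7% and 89% of runs with zero change.

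**Reading 2: program group as factor, adjusted for T1.** The F test asks whether nine groups that all received the program differ from one another. It rejected in 4–6% of runs at 0, 0.3 and 0.5 SD alike, so it cannot see a common change.

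**Reading 3: repeated measures with age as an uncentred covariate.** If age is allowed to modify change, the time term refers to age 0. With mean age 13.5 and SD 1.44 (uniform range 4.99/√12), its standard error is inflated by about √(1 + 13.5²/1.44²) ≈ 9.4. At 0.3 SD it rejected in 6–8% of runs.

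**Reading 4: change score or repeated measures with a centred covariate.** This does test mean change. With centred age it rejected in 5–6% of runs at zero change and in 79% to more than 99% at 0.3 SD. With T1 itself centred at its sample mean, rejection at zero change was 6–10%. The excess arises because the model treats the sample baseline mean as fixed.

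**Benchmark: paired test of T3–T1.** It rejected in 5–6% of runs at zero change. Power at 0.3 SD was 79%, 92% and more than 99% for r = 0.4, 0.6 and 0.8. The change detectable with 80% power is (1.960 + 0.842) × √(2(1 − r))/√101, which is 0.31, 0.25 and 0.18 SD.

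**LCQ.** One measurement at week 6 gives no baseline, no change score and no comparator. No arithmetic applies.

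**The case against.** The strongest reply is that the article is condensed. It states a pretest-posttest design, gives weeks 1 and 9 as the time points and speaks of changes in the outcomes. A repeated-measures model with time as the within-girl factor is then a natural reading of the ANCOVA sentence, and centring and covariate lists are normally left to an analysis plan. The study is also exploratory, and the Discussion already says that cause and effect cannot be determined.

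Much of this stands. A reader might infer that ANCOVA leaves nothing at all to test here. That goes too far, because Reading 4 works. A reader might also infer that the plan carries a false-positive rate of 89–100%. The documents do not support that: the figure belongs to one assumed uncentred model and to reading its intercept as the result, and the article states neither. Nor is the baseline slope for a change score bound to be non-zero whenever the correlation is below 1. It equals r × SD(T3)/SD(T1) − 1, which is 0 for r = 0.7 with SDs of 0.7 and 1.0, so that claim needs equal variances. How girls absent at week 9 are handled is a separate and secondary matter on which this section is silent.

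The reply does not remove the point. The complaint is about the method the article does name, for every outcome, and not about detail left out. It also cannot rescue the LCQ: no choice of factor or centring creates a change score from one measurement.

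**Conclusion.** The point holds in this form: the stated method does not fit a single-arm pretest-posttest design unless it is redefined as a model of T3–T1 change, and the article does not define it so. It cannot assess change in the LCQ at all.

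The structural argument needs no assumed values. The simulated percentages are illustrations only. They rest on assumed correlations, mean, SD and age distribution, on no clustering or dropout, and on 101 girls analysed. That last number is not established, since girls could join the program without joining the research. Under those values, the choice of reading moves the chance of detecting a 0.3 SD change from about 5% (program-group F test) to 79% or more (paired test).

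Even the right test shows change and not a program effect, as the Discussion concedes.

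**What to change.** Replace the ANCOVA sentence with the following.
- For the Physical Activity Questionnaire for Children, the Self-Compassion Scale, the Child and Adolescent Social Support Scale and the sport commitment and enjoyment scores, estimate the mean T3–T1 change with its 95% CI, from a paired analysis or a linear mixed model with time as the effect.
- Mean-centre any covariate, such as age.
- Account for clustering by program group. A random group-by-time effect is one option, not a requirement, and with nine groups its variance will be poorly estimated.
- Report the LCQ descriptively.
- Word objectives 1 and 2 as within-girl change, except for the LCQ, in line with the limitation already in the Discussion.

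The cost is a small change of analysis wording. No new data are needed.

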#### Program Components

The GUM intervention was a pragmatic PA and psychosocial program designed specifically for at-risk adolescent girls. Components of the self-determination theory, particularly autonomy, competence, and relatedness, were integrated throughout the intervention because these are known to affect intrinsic motivation and engagement in PA, especially among underserved youth [11,33]. The GUM intervention consisted of 9 weekly, group-based, 90-minute face-to-face sessions that were cofacilitated by a trained researcher and a registered social worker from a partnering community organization or key stakeholder. The partnering stakeholder was a nonprofit organization with the goal of bringing an end to violence and poverty and seeking justice for children and women. This nonprofit organization works extensively with adolescent populations, particularly those categorized as at risk. Each GUM group consisted of 7 to 14 at-risk adolescent girls from participating schools. Smaller groups were desired in order to create an intimate and supportive environment and provide a greater opportunity for participants to get acquainted with each other and the program facilitators.

Within each of the weekly 90-minute program sessions, 45 minutes of PA were delivered by a trained researcher and 45 minutes were allocated to social worker–led discussions on various psychosocial topics. Examples of physical/sport activities included on-campus activities such as yoga, team obstacle courses, and soccer, or off-campus activities such as rock climbing, self-defense classes, and fitness classes. Examples of psychosocial topics that were discussed within each group included healthy relationships, conflict resolution strategies, substance abuse issues, sexuality, and gender issues. Table 2 outlines the components of the GUM intervention.

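### The stated ANCOVA has no term for group or school, although the programme ran in 9 interacting groups within 5 schools; with any positive within-group correlation the .05 level is exceeded

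*Protocol article*

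**What the plan says.** The Data Analysis section gives one quantitative method for every outcome: changes in physical activity, self-compassion, social support, perceived leader supportiveness, and sport commitment and enjoyment "will be analyzed using an analysis of covariance statistical design". It adds that "The level of significance will be set at α=.05" and names SPSS. It names no group or school term, random effect or cluster-adjusted standard error.

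The structure of the data is described elsewhere. Under Participants, Setting, and Recruitment: "A total of 101 participants forming 9 groups were recruited from 5 schools throughout the region". The same section says that each group had its own start date and that groups from one school never ran at the same time. Table 1 lists the nine group sizes. Program Components describes "9 weekly, group-based, 90-minute face-to-face sessions that were cofacilitated by a trained researcher and a registered social worker" and explains that groups were kept small to "create an intimate and supportive environment and provide a greater opportunity for participants to get acquainted with each other and the program facilitators".

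The limitations in the Discussion cover self-report, the absence of a control group, the lack of long-term follow-up and generalizability. Clustering is not among them.

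**The concern.** Ordinary ANCOVA treats the residuals of different girls as independent. Here, girls in one group share sessions, school and calendar period. Relatedness is one of the mechanisms that the programme builds on, and social support and leader behaviour are among its primary outcomes. Some positive correlation within groups is therefore plausible, both for the changes from T1 to T3 and for the LCQ ratings that a group gives the facilitators it shares.

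If that correlation exists and is ignored, the analysis counts more independent information than it has. Confidence intervals are too narrow and the false-positive rate rises above the stated level. With no control arm, these tests are the main quantitative evidence on effectiveness, and the Results section plans to send the findings to stakeholders and government agencies.

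**Working it through.** **Inputs from the article.** Table 1 group sizes: 13, 11, 13, 9, 7, 14, 10, 11, 13. Five schools. α = .05, taken as two-sided because the article does not say.

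**Assumptions.** The article gives no ICC, so a range is used. It does not say what contrast the ANCOVA tests, so the check uses a one-sample test of the mean T1 to T3 change. All 101 girls are taken as analysed.

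**Step 1, the article's own figure.** The nine sizes sum to 101, as stated. With ICC = 0, the test on 101 independent girls holds its level (0.051 in 40,000 simulated data sets).

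**Step 2, design effect for unequal groups.** The squared sizes sum to 169 + 121 + 169 + 81 + 49 + 196 + 100 + 121 + 169 = 1175. The size-weighted mean is 1175/101 = 11.63, so

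DE = 1 + (11.63 − 1) × ICC = 1 + 10.63 × ICC.

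**Step 3, consequences.** The standard error is too small by a factor √DE, the effective N is 101/DE, and the actual type I error is 2 × [1 − Φ(1.96/√DE)]. For ICC 0.05: DE = 1 + 10.63 × 0.05 = 1.53, √DE = 1.24, 101/1.53 = 66, and 1.96/1.24 = 1.58, which gives 0.113.

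| Assumed group ICC | DE | √DE | Effective N | Type I error, formula | Type I error, simulated |
|---|---|---|---|---|---|
| 0.01 | 1.11 | 1.05 | 91 | 0.062 | 0.061 |
| 0.02 | 1.21 | 1.10 | 83 | 0.075 | 0.073 |
| 0.05 | 1.53 | 1.24 | 66 | 0.113 | 0.114 |
| 0.10 | 2.06 | 1.44 | 49 | 0.172 | 0.174 |
| 0.20 | 3.13 | 1.77 | 32 | 0.268 | 0.275 |

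**Step 4, correlation by school instead.** With five equal schools assumed, the mean size is 101/5 = 20.2 and DE = 1 + 19.2 × ICC. ICCs of 0.01, 0.05 and 0.10 give DE 1.19, 1.96 and 2.92, and type I errors of about 0.07, 0.16 and 0.25.

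**Step 5, possible repairs, simulated.**
- Group as a fixed factor does not restore the level for inference beyond these nine groups: 0.062 at ICC 0.01, rising to 0.320 at 0.20.
- A t-test on the nine group means (8 df, critical t 2.31) holds 0.048 to 0.051 when correlation is by group only.
- That same test does not hold if girls also correlate by school. With groups assigned to schools as 2-2-2-2-1 (assumed; the article gives no mapping), its error is about 0.09 at a school ICC of 0.05 and about 0.11 at 0.10.

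**The case against.** The strongest reply is that this turns silence into a statement. The article is condensed. It never calls the girls independent and gives no factor, covariate or unit of analysis. ANCOVA does not exclude a group or school term, and a fuller plan may contain one. This stands in part: a reader might infer that the plan declares 101 independent girls, or an error term with some 99 degrees of freedom, and the article says neither. But it does fix a named method for every outcome, and in its usual form that method assumes independence. Step 5 shows that the simplest extension, a fixed group factor, would not be enough.

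A second reply is that the error rates belong to a test which the article does not name and to ICCs which it does not give. That also stands. A reader might take a figure such as 0.17 as the plan's known false-positive rate; it is conditional, and at ICC 0.01 the excess is small. The social support scale asks about parents, teachers, classmates and close friends, not about the programme group as such. Shared facilitators raise within-group correlation only if they, or their effect, differ between groups. The number analysed may also be below 101, since the research component was optional.

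Third, a reader might apply the change-score figures to every outcome. They do not fit the LCQ, which was given only at week 6 and so has no change, although its ratings may cluster too.

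Finally, the study is labelled exploratory, and its Discussion concedes that cause and effect cannot be determined. This lowers the stakes but does not correct a standard error that is too small.

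**Conclusion.** The point holds as a conditional one. The analysis as worded does not reflect the documented grouping, and carried out as an ordinary individual-level ANCOVA it exceeds .05 whenever outcomes correlate positively within groups or schools. For a one-sample mean change in all 101 girls, the type I error runs from about 0.06 at a group ICC of 0.01 to about 0.27 at 0.20. The direction needs only a positive ICC; the size cannot be fixed from the article.

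The article does not support the stronger conclusions that the level is certainly breached by a known amount, or that nine group means are sure to be independent units: the groups are nested in five schools.

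Severity: should-fix, because the study is exploratory and uncontrolled.

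**What to change.** For outcomes measured at T1 and T3, state that the mean change will be estimated with a mixed model that has a random group effect on the change. Put school in the main model too, as a random effect or as the top-level unit. Use Satterthwaite or Kenward-Roger degrees of freedom and report the ICC. Cluster-robust standard errors without a small-sample correction are no substitute with 9 groups or 5 schools, because they would themselves be too small.

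As checks, add a t-test on the nine group-mean changes (8 df), stated to be valid only if school-level correlation is negligible, and one on the five school means (4 df). For the LCQ, report the week 6 mean with a cluster-adjusted interval in place of a test of change. Add clustering to the limitations.

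The cost is analysis wording only: group and school are already known for every girl, so no new data are needed. Intervals become wider and the degrees of freedom few. The critical t is about 2.31 with 8 df and 2.78 with 4 df, against 1.98 for 101 independent girls.
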